## Abstract

**Introduction:**

Colistin is a last-resort antimicrobial used to treat infections caused by multidrug-resistant Gram-negative bacteria in humans. In Indonesia, widespread detection of colistin use and resistance in commensal *Escherichia coli* from poultry, particularly broilers, led to a national ban on its use in livestock effective since July 1st, 2020. However, the impact of this policy intervention on colistin resistance in both humans and livestock has not yet been evaluated. The COINCIDE study aims to investigate the ban's effect on colistin resistance, compliance, and transmission dynamics of resistance between humans and poultry.

**Methods and analysis:**

COINCIDE will: (i) assess phenotypic and genotypic colistin resistance in *E. coli* from humans and poultry; (ii) estimate transmission of colistin resistant *E. coli* between humans and animals; (iii) explore colistin and antimicrobial use (AMU) at the community level; (iv) identify social and cultural factors driving AMU; and (v) strengthen multisectoral One Health collaboration. Post-ban sampling will be conducted in three districts of Central Java Province (Klaten, Karanganyar, and Sukoharjo), where pre-ban samples were already available. We will recruit participants from primary healthcare centers (PHC) (*n* = 683), poultry farmers (*n* = 120), and visit a total of 60 small-scale layer farms. Broiler isolates (*n* = 2865) from Indonesia's routine antimicrobial resistance (AMR) surveillance (2018–2023) will also be included. In terms of sample collection, post-ban samples will include rectal swabs from patients visiting PHC and farmers and boot swabs from small-scale layer farms. Colistin resistance will be screened using CHROMagar COL-APSE agar medium and confirmed by broth microdilution. Results of long-read whole-genome sequencing will identify resistance mechanisms and transmission pathways. A qualitative ethnography work will include participant observation and informal conversations during field visits, alongside in-depth interviews with healthcare professionals and stakeholders. “Drug bag” method interviews will assess antimicrobial use, access, and drivers at the community level. Simulated patient visits to pharmacies and local shops (*warung* or *toko obat*), and interviews with agrovet outlets and poultry shops will be conducted to evaluate compliance with antimicrobial sales regulations.

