### Study design and setting

3.1

The COINCIDE study adopts a cross-sectional comparative design embedded within a One Health framework, supporting simultaneous assessment of colistin resistance and AMU across human and poultry sectors. Sampling will be conducted prospectively and compared with archived pre-ban data collected in 2014. Three districts in Central Java, Sukoharjo, Klaten, and Karanganyar are selected as study locations to maintain consistency with pre-ban data collection from layer farms in Central Java, Indonesia (Fig. 4). These districts provide a diverse social, cultural, and economic setting, where small-scale livestock farming, local health-seeking behaviors, and routine antimicrobials use create an ideal context for studying community- and farm-level antimicrobial practices.

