### Sample size and sampling strategies

3.2

To detect a meaningful reduction in colistin resistance from an estimated 15% before the ban to 10% afterward, power calculations indicated the need to analyze at least 683 *E. coli* isolates and risk factor surveys from both human and poultry sources. The retrospective (pre-ban) isolates include 577 archived human isolates from primary health care centers (PHC), 2182 broiler surveillance isolates, 513 layer chicken isolates, and 63 layer farmer isolates from 2014. Regarding the prospective sampling, human participants (*n* = 683) will be recruited from PHC, with eligibility criteria including adults over 18 years without current diarrhea or vomiting, who provide informed consent for rectal swab collection. Random selection via raffles of clinic attendees meeting these criteria will be used to minimize selection bias.

Up to 60 small-scale laying hen farms will be sampled to get an estimated 683 bacterial isolates, identified through local livestock office records. The small-scale layer farm is defined as having fewer than 10,000 layer chickens. Boot swabs will be collected from poultry houses. Farm workers (two or three from each farm, *n* = 120) will also be invited to provide rectal swab samples, enabling paired human-animal analysis. We will document recruitment and refusal rates in each setting to assess potential selection bias. All field teams will follow standard operating procedures developed by the COINCIDE consortium for sample labeling, cold-chain maintenance, and data recording to ensure quality and traceability. Additionally, available AMR data from the national broiler surveillance program from 2018 to 2023 will be incorporated. Within this surveillance program, approximately 800 caecal samples are collected from broilers per year via regional Disease Investigation Centers. From these samples, *E. coli* is isolated, and these isolates are tested for antimicrobial susceptibility including colistin using broth microdilution. These data provides a national perspective on resistance trends before and after the ban.

The complete COINCIDE sample scheme is also illustrated in Fig. 3.

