### Laboratory protocols

3.4

Laboratory protocols will be developed iteratively in collaboration with local laboratories, given options for capacity building and limited resources available. Human rectal swab and poultry/environmental boot swab samples will be cultured for *E. coli* on MacConkey agar. For human isolates, bacterial identification will be done using an automatic machine (VITEK® 2 COMPACT, bioMerieux). One presumptive *E. coli* colony per human sample and 15 *E. coli* isolates from boot swabs from layer farms will be selected. For animal isolates, *E. coli* isolates will be confirmed using biochemical tests. In parallel, isolates will be plated on CHROMagar™ COL-APSE (selective medium) in a tailor-made spot-test protocol that allows screening up to eight isolates per plate to screen for colistin-resistant growth. The protocol has been published on https://www.protocols.io, and the video protocol is available online (https://youtu.be/KC1x9u4d02g). Each batch of CHROMagar plates will include a colistin-susceptible *E. coli* strain (ATCC 25922) and a known *mcr*-1-positive *E. coli* as negative and positive controls, respectively. All isolates that grow on CHROMagar (presumptive colistin-resistant) will be tested using automated broth microdilution system (Sensititre, ThermoFisher) to determine colistin MIC, following the most recent EUCAST/CLSI standards. MIC results will be interpreted using the EUCAST MIC and ECOFF database. The ECOFF for colistin resistance in *E. coli* is ≤2 mg/L [42]. All isolates will be catalogued and stored at −80 °C in laboratories in Indonesia. Colistin-resistant *E. coli* isolates will be sequenced using Oxford Nanopore Technologies (ONT) long-read sequencing. DNA extraction, library preparation, and sequencing will be performed in-country by trained local staff. Where relevant, the Microbiology Investigation Criteria for Reporting Objectively (MICRO) framework will be followed in reporting [43].

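### The transmission objective claims more than single cross-sectional swabs of resistant isolates can show: they support strain sharing, not a rate, a direction or exclusion of a common source

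*Protocol article*

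**What the plan says.** **The claim.** Objective (ii), in the abstract under Methods and analysis, is to "estimate transmission of colistin resistant *E. coli* between humans and animals". The abstract's Introduction says that the study aims to "investigate the ban's effect on colistin resistance, compliance, and transmission dynamics of resistance between humans and poultry". Section 3.5 adds that bioinformatics will trace transmission dynamics, using phylogenetic and plasmid analysis.

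**The design.** Section 3.1 states that the study "adopts a cross-sectional comparative design embedded within a One Health framework", and continues: "Sampling will be conducted prospectively and compared with archived pre-ban data collected in 2014". No repeat swab of the same person or farm is described.

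**Isolates and sequencing.** Section 3.4 states: "One presumptive *E. coli* colony per human sample and 15 *E. coli* isolates from boot swabs from layer farms will be selected". On sequencing, it says: "Colistin-resistant *E. coli* isolates will be sequenced using Oxford Nanopore Technologies (ONT) long-read sequencing". Sequencing of susceptible isolates is not mentioned.

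**The human-animal link.** Section 3.2 provides the pairing: "Farm workers (two or three from each farm, *n* = 120) will also be invited to provide rectal swab samples, enabling paired human-animal analysis". From 2014 it lists 63 layer farmer isolates and 513 layer chicken isolates, without saying whether they can be linked by farm.

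**The concern.** To estimate transmission, one needs to observe acquisitions or have some other basis for inferring them. A worker and a flock swabbed in one round, both yielding the same resistant strain, fit four histories:

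- spread from bird to human;
- spread from human to bird;
- a common source, such as water or a supplier;
- a clone or plasmid circulating across the district.

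The design, the number of colonies picked and the isolates to be sequenced are all fixed in the article. An analysis plan written later cannot recover the timing of acquisition from them.

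The practical risk lies in the conclusion. The study is meant to inform policy. If sharing is reported as transmission, background circulation of a common strain may be credited to the farm. If fewer matches are seen after the ban, this may be read as interrupted transmission.

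**Working it through.** **1. The plan's own sample size.** Section 3.2 gives 683 isolates to detect a fall from 15% to 10%. Taking two-sided alpha 0.05 and 80% power (neither sidedness nor power is stated) and unpooled variance:

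(1.96 + 0.8416)² × (0.15 × 0.85 + 0.10 × 0.90) / 0.05² = 682.85, so 683 per group.

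The figure reproduces. It sizes a comparison of prevalence; no figure is given for transmission or sharing.

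**2. Matching without farm-level transmission (illustration).** Assumptions: 10% resistance in flock isolates (the planning value after the ban), one clone making up 30% of resistant isolates (not in the documents), and independent isolates. An isolate is resistant and of that clone with probability 0.10 × 0.30 = 0.03. Isolates per farm are 683/60 = 11.4 from section 3.2, or 15 from section 3.4.

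- 11.4 isolates: 1 − 0.97^11.4 = 0.29
- 15 isolates: 1 − 0.97^15 = 0.37

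A worker carrying the clone would therefore find it in the own flock 29% to 37% of the time by background alone. Clustering of isolates within a farm would lower this, and so would a relatedness threshold finer than clone membership. A rarer clone also gives a smaller figure.

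**3. Paired data after the ban.** Assume that 10% also applies to workers. Then 120 × 0.10 = 12 workers would yield a resistant isolate (6 to 24 at 5% to 20% resistance). A farm yields at least one resistant flock isolate with probability 1 − 0.9^11.4 = 0.70 to 1 − 0.9^15 = 0.79. Under independence, 12 × 0.70 = 8.4 to 12 × 0.79 = 9.5 resistant workers would be on such a farm. If 3 of 12 shared a strain with their flock, the exact 95% interval would be 5% to 57%.

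**4. Before versus after.** With 15% applied to the 63 farmer isolates from 2014, 63 × 0.15 = 9.45, so about 9 resistant farmers against 12. Power to separate 50% from 25% sharing with 9 versus 12 is about 22%.

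**5. Effect of prevalence on match counts.** If resistance fell from 15% to 10% independently in humans and poultry, the share of human-poultry isolate pairs with both resistant would go from 0.15 × 0.15 = 0.0225 to 0.10 × 0.10 = 0.0100. That is a fall of 56% with the sharing process unchanged.

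**6. One colony per human.** If resistant *E. coli* make up 10% of a carrier's *E. coli* flora, one colony detects them with probability 0.10; fifteen colonies would do so with probability 1 − 0.9^15 = 0.79. The absence of a match is therefore weak evidence of no sharing.

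**The case against.** **The text names neither a rate nor a direction.** Objective (ii) speaks of transmission between humans and animals, and the sentence on the ban can be read as a list of three topics. This is fair as to wording. But an aim to estimate transmission promises a quantity, and the natural reading of the other sentence is that the ban's effect on transmission dynamics will be studied.

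**Analysis detail may sit in the full protocol or analysis plan.** This stands: the lack of a stated threshold, reference level or test in an article is no fault. The point is confined to what the article fixes, namely single sampling, colony numbers and which isolates are sequenced.

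**The design can address background circulation.** A reader might infer that the data cannot show sharing above background at all. The documents do not support that. Up to 60 farms and the attendees of primary health care centers (PHC) are sampled, and their resistant isolates fall under the same sequencing statement. A within-farm versus between-farm comparison is therefore possible, though imprecise and unable to exclude a source shared by a farm's workers and birds.

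**The plan does not say that match counts will be compared between periods.** Correct. Step 5 is a caution on interpretation. Fewer resistant isolates in poultry may also mean less transmission of resistant *E. coli*, so a fall in matches need not be an artefact.

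**Participants' exposure is recorded.** Section 3.3.1 collects animal contact, diet, and water and sanitation. It would be wrong to infer that PHC participants have no exposure data; what is not stated is a link to a sampled flock.

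**Sequencing resistant isolates suits an objective about resistant *E. coli*.** This also stands. It limits what can be learned but does not conflict with the objective.

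**Conclusion.** The stated aims exceed the design. With single swabs, one colony per person and sequencing stated only for resistant isolates, the study can describe sharing of strains and plasmids and can test, with little precision, whether sharing is greater within farms than between them. It cannot give a transmission rate, the direction within a worker-flock pair, or exclusion of a common source.

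The background match of 29% to 37% is an illustration and rests on the assumed 30% clone, 10% resistance and independent isolates. The sparse before/after comparison, about 9 versus 12 resistant farmers, assumes that the planning rates of 15% and 10% apply to farmers. The mismatch between aim and design depends on none of these figures. The planned prevalence comparison is not affected by this point.

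**What to change.** 1. Reword objective (ii) and the corresponding aim in the abstract's Introduction as genomic relatedness and sharing of resistant strains and *mcr* plasmids between layer-farm workers and flocks, without direction or rate.
2. For the post-ban paired analysis in section 3.2, define the measure as the excess of within-farm over between-farm worker-flock matches in the same district. Fix the relatedness threshold in advance and obtain the reference distribution by permuting farm labels within district.
3. State that a change in match counts between periods will not be read as changed transmission. Keep any before/after comparison of sharing descriptive, and make it only if the 2014 farmer and layer isolates can be linked by farm.
4. Report similarity between PHC and poultry isolates as descriptive.

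**Cost.** Rewording, plus a permutation analysis on sequences already planned; no new samples or sequencing. The downside is a more modest claim and an imprecise estimate of excess sharing, which still cannot exclude a common source on the farm.

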**Conclusion:**

By integrating microbiological, epidemiological, policy, and social science data, findings from the COINCIDE study will provide a strong scientific basis to inform AMR policies in Indonesia, with potential significance to inform other countries across Southeast Asia.

## Introduction

1

Antimicrobial resistance (AMR) remains a critical and growing threat to global public and animal health, economic stability, and health security. The 2024 high-level meeting on AMR at the United Nations General Assembly reaffirmed the continued political commitment to addressing this complex, cross-border One Health issue [1]. Since the adoption of the World Health Organization (WHO) Global Action Plan on AMR in 2015, member states have increasingly recognized the urgency of combating the AMR crisis and advanced their responses by developing and implementing national action plans on AMR (NAP-AMR). The Tracking AMR Country Self-Assessment Survey (TrACSS) reported a significant rise in NAP-AMR development, from 41% of member states in 2016–2017 to 88% by 2023–2024 [2]. Despite these efforts, AMR remains a significant burden, particularly in Southeast Asia, South Asia, and Sub-Saharan Africa [3]. Indonesia exemplifies this challenge, with its unique geographical and socioeconomic factors driving high antimicrobial use (AMU) in both humans and animals [4].

Indonesia is the world's fourth most populous country, consisting of over 17,000 islands, and approximately 285 million people [5]. Its large human population is complemented by substantial livestock populations: 3.71 billion poultry (mainly 84.9% broilers, 11.1% layers, followed by 4.0% free-range chickens), along with 4.11 million swine, and 11.75 million cattle [6]. Driven by population growth and rising demand for affordable protein, the broilers population alone was expected to grow from 3.28 billion head in 2024 to 3.4 billion head in 2025 [7], [8]. National initiatives such as the Makan Bergizi Gratis (MBG) program, which provides free nutritious meals to schoolchildren and pregnant women, further intensify food production pressures [9]. Meanwhile, outbreaks of infectious diseases including avian influenza, lumpy skin disease, African swine fever, and foot-and-mouth disease threaten livestock health and productivity [10]. Alarmingly, AMU in Indonesian livestock was projected to increase by 202% between 2010 and 2030 if current trends continue, highlighting the urgent need for effective strategies to curb AMR within a One Health framework [11].

One promising strategy to reduce AMR in One Health context is the withdrawal and restriction of antimicrobials used in animals through comprehensive policy and regulatory action [12]. Globally, regions such as Europe and North America have successfully reduced AMU and AMR by banning antimicrobial growth promoters (AGPs) and prophylactic use in livestock [13], [14]. In Indonesia, a key milestone was the 2017 NAP-AMR, confirming its commitment to advancing multisectoral One Health collaboration. Building on this NAP-AMR, the Indonesian government banned AGPs in 2018 under the Livestock and Health Law, which states “every person is prohibited from using feed ingredients mixed with certain hormones or antibiotics” [15]. More recently, in response to the detection of colistin use and colistin-resistant *E. coli* in healthy poultry through national AMR surveillance, Indonesian issued a ban on colistin use in livestock in 2020 [16], [17]. A summary of global and national interventions is presented in Fig. 1.

**Fig. 1 f0005:**
[figure not shown]
Roadmap showing key milestones in the withdrawal and restriction of antimicrobial use in animals through global policies and legislation, aimed at reducing antimicrobial resistance in humans and animals [13], [14], [18], [19], [20], [21], [22], [23], [24], [25].

Colistin, also known as polymyxin E, is a last-resort antimicrobial critical for treating multidrug-resistant Gram-negative infections in humans. Although the clinical use of colistin in humans was limited in the 1980s due to toxicity concerns, the rise of carbapenem-resistant pathogens has renewed its importance [26]. The WHO classified colistin as a highest priority critically important antimicrobial (HP-CIA) for human medicine. However, in many Asian countries, including Indonesia, colistin has been widely used in livestock as a growth promoter and for prophylaxis, further contributing to driving colistin resistance development [27]. The discovery of plasmid-mediated mobilized colistin resistance (*mcr*) genes in 2016 transformed understanding of colistin resistance and AMR transmission, as these genes can spread rapidly between bacteria [28]. In response, countries such as China have restricted colistin use in agriculture, leading to measurable declines in resistance among both animals and humans [24]. Multiple studies from other countries including China, Japan, Portugal, and Spain also showed that banning or restricting colistin use in agriculture leads to a significant reduction in colistin resistance and *mcr*-1 gene prevalence among both animals and humans [29], [30], [31], [32], [33], [34], [35] (Table 1). In the case of Thailand where colistin was banned in 2017, Khine et al. (2022) reported that colistin-resistant *E. coli* prevalence in pigs dropped significantly from 60% in 2017 and 50% in 2018 to 3% in 2019, before rising again to 33% in 2020. In humans, colistin resistant *E. coli* were only detected in 2017 and disappeared in subsequent years [36]. The circulation of colistin resistance after the ban was observed in places like Thailand and it may be due to weak law enforcement and poor compliance with the colistin ban, as regulatory frameworks in Southeast Asia region are likely to be insufficient to ensure effective implementation [37].

**Table 1 t0005:** Prevalence change of *mcr* genes before colistin ban and colistin resistance across countries and sample types (MIC = minimum inhibitory concentration).

Country	Sample (Bacterial species)	Colistin resistance	Study period	Prevalence change (%)	Reference
China	Human hospital patients (*E. coli*)	*mcr-1*	2016–2019	14.3 → 6.3	[24]
China	Human community (*E. coli*)	MIC	2015–2019	1.7 → 1.3	
China	Pigs (*E. coli*)	MIC	2015–2018	34.0 → 5.1	
China	Chickens (*E. coli*)	MIC	2015–2018	18.1 → 5.0	
China	Pigs (*E. coli*)	*mcr-1*	2015–2019	38–45 → < 2	[29]
China	Broiler chickens (*E. coli*)	*mcr-1*	2016–2019	12.6 → 0.9	[35]
China	Pigs (*E. coli*)	*mcr-1*	2016–2018	45 → 19	[38]
China	Pigs (*E. coli*)	*mcr-1*	2017–2018	86.4 → 5.6	[34]
China	Human healthy volunteers (*E. coli*)	*mcr-1*	2018–2019	11.5 → 2.4	[30]
Japan	Pigs (*E. coli*)	*mcr-1*	2017–2018	17.8 → 6.7	[31]
Portugal	Poultry meat (Enterobacterales)	*mcr-1*	2020–2021	60 → 24	[33]
Spain	Healthy pigs (PCR only)	*mcr-1*	2017–2021	54 → 17	[32]
Thailand	Piglets and human (*E. coli*)	*mcr-1*	2017–2020	Piglets 60 (2017) → 3 (2019) → 33 (2020) Human 40 (2017) → 0 (2020)	[36]

Colistin was banned for use in livestock in Indonesia on July 1st, 2020. This policy ban provides a unique and timely opportunity to assess the effectiveness of such a policy in reducing AMR given its large poultry sector, prior colistin use and distinct regulatory and sociodemographic context (Fig. 2).

**Fig. 2 f0010:**
[figure not shown]
Timeline of colistin discovery, use, resistance, regulatory actions, and the origin of the COINCIDE consortium addressing colistin resistance (1947–2025). MDR, multidrug resistance.

The COINCIDE study represents a transdisciplinary, multisectoral One Health collaboration involving medical doctors, microbiologists, veterinarians, epidemiologists, and social scientists, based at universities, research institutes, non-governmental organizations, and government bodies in Indonesia, Belgium, Canada, and the Netherlands. This consortium aims to evaluate the impact of the colistin ban on colistin resistance in *E. coli* from both poultry and human populations, integrating molecular epidemiology, microbiology, and social science research to understand the social and behavioral drivers of colistin and broader AMU and resistance.

